## 6. METHODS

### 6.1 Study parameters/endpoints

#### 6.1.1 Screening measures

##### **Screening measure: Intelligence**

##### **Instrument: Wechsler Intelligence Scale for Children III (WISC-III)**

Children must meet the following criterion: TIQ  $\geq 80$ . A previous assessment of IQ dating back less than 2 years with tests being comparable with the WISC-III must be available. If no assessment of IQ dating back less than 2 years is available, this criterion will be checked by administering two subtests (i.e. vocabulary and block design) of the Wechsler Intelligence Scale for Children III (WISC-III) (Wechsler, 2005). The norm score of the subtest will be multiplied with 5 and summed up. Afterwards with this total score the TIQ can be estimated. This composite score has satisfactory reliability ( $r = 0.91$ ) and correlates highly with the full-scale IQ score (Dovis et al., 2010; Sattler, 2001).

##### **Screening measure: DSM-IV ADHD diagnosis and co morbidity**

##### **Instrument: Kiddie-SADS-Present and lifetime version (K-SADS)**

The K-SADS (Puig-Antich & Chamber, 1978; Reichart, Wals & Hillegers, 2000) is a semi structured interview designed to diagnose psychiatric problems using the DSM-IV criteria. For this study the parents are interviewed to reconfirm the ADHD diagnosis and guarantee the ADHD diagnosis is made in a standardized way. In addition, children who are addicted to drugs, alcohol and/or gaming, have CD or severe acute psychiatric disorders such as psychotic disorder, major depressive disorder or mania will be excluded on basis of an interview with parents and in doubt this will be checked with the K-SADS. Duration of the interview is about 30 minutes.

##### **Screening measure: Severity of symptoms**

##### **Instrument: VvGK filled out by parents/legal guardians (Attachment A.)**

The VvGK is originally developed by Pelham, Gnagy, Greenslade and Milich (1992) and translated to Dutch by Oosterlaan and colleagues (2000). It is a questionnaire which contains both a parent and a teacher version. For this study only the parent version will be used. The VvGK measures if and to what extent symptoms of ADHD, ODD and CD are present in children and can be used as a diagnostic tool. It consists of 42 items measuring in four domains: attention deficit, hyperactivity and impulsivity, oppositional behaviour, and conduct disorders. Completing the questionnaire takes about ten minutes. Good psychometric values

are reported by the COTAN: Norms: sufficient, Reliability: sufficient, Construct validity: good, Criterium validity: not researched.

### **Screening measure: General child characteristics**

**Instrument: Self-constructed questionnaire** filled out by parents/legal guardians  
(Attachment.B)

To collect information about the background and medical history of the children a general questionnaire is given to the parents/legal guardians. There is also a question in this questionnaire about the current support for the parents/legal guardians (such as psycho education or parent support groups).

## **6.1.2 Outcome measures**

### **Outcome measure: Planning**

**Instrument: BRIEF** filled out by parents/legal guardians and teachers (subscale: Plan/Organise) (Attachment.C – parents and Attachment I - teachers)

The Behaviour Rating Inventory of Executive Function (BRIEF) is a screening list to assess executive functioning in the home and school environment in children 5-18 years of age (Smidts & Huizinga, 2009). The questionnaire contains 86 items in eight non-overlapping clinical scales and two validity scales. These theoretically and statistically derived scales form two broader Indexes: Behavioural Regulation (three scales: Inhibit, Shift, Emotional Control) and Metacognition (five scales: Initiate, Working Memory, Plan/Organise, Organisation of Materials, Monitor), as well as a Global Executive Composite score. The answers are scored on a 3-point Likert scale (never – sometimes - often). It takes approximately 30 minutes to fill in the questionnaire. The Dutch version of the BRIEF contains norms of a representative sample of children in regular education. The BRIEF has a good reliability and construct validity (Elling & Minderaa, 2010).

### **Outcome measure: Planning**

**Instrument: Tower Test** performed by the child

The Tower Test is a subtest of the Delis-Kaplan Executive Function System battery and tries to measure several executive functions such as spatial planning, rule learning, inhibition of impulsive responding and establishing and maintaining instructional set in children and adults from 8 to 89 years. The material consist of 5 disks that vary in size from small to large and a board with three vertical pegs. The objective is to move all the disks to the rod on the right, observing the following rules: only one disk may be moved at a time, a larger disk may not be placed on top of a smaller disk and disks must always be placed on one of the rods. Children

have to build a tower in as few as possible steps and as quickly as possible. Outcomes vary from number of rule violations, total number of moves to completion time, whereby various ratios can be calculated. It takes around 30 minutes to administer the test. This test is not judged by the COTAN but research into the Tower of London Test indicates that this is a reliable and valid method to measure planning skills in children (Unterrainer et al., 2004).

**Outcome measure: Time management**

**Instrument: Self constructed questionnaire** filled out by parents/legal guardians and teachers (**Attachment.D – parents and Attachment I - Teachers**)

The time management scale contains 11 descriptions of time management behaviour. Parents/legal guardians and teachers are asked to rate the time management skills of their child on a 10 point Likert scale (ranging from true – not true). From the pilot study results it appeared that this questionnaire is reliable (Chronbach's alpha = 0.85).

**Instrument: “It is about time” questionnaire (Barkley, 1998)** filled out by parents/legal guardians (**Attachment.E**)

The “It is about time” questionnaire consist of 25 questions concerning time perception and time management. Parents/legal guardians and teachers are asked to rate the time perception and time management skills of their child. Completing the questionnaire takes about ten minutes.

**Outcome measure: Social behaviour**

**Instrument: Social Skills Improvement System (SSIS) Rating Scales (subscale social skills)** filled out by parents/legal guardians and teachers (**Attachment.F – parents and Attachment I - Teachers**)

The Social Skills Improvement System (SSIS) Rating Scales assists (Gresham & Elliot, 2008) in screening and classifying children with significant social skills deficits. There are 3 different rater forms: parent, teacher and student. The SSIS rating Scales assesses 3 domains: 1) Social Skills, 2) Problem Behaviour and 3) Academic Competence. The Social Skills questions are divided in 7 subdomains: communication, cooperation, assertion, responsibility, empathy, engagement self-control. The Problem Behaviour questions are divided over 5 subdomains: externalizing, bullying, hyperactivity/inattention, internalizing, autism spectrum. The SSIS rating scales appeared to have a high internal consistency reliability, as well as a high test retest reliability.

**Outcome measure: Social behaviour**

**Instrument: Social-Cognitive Skills Test (SCVT)** performed by the child.

This instrument measures eight social cognitive skills of children between 4 and 12 years of age. The eight age-related social cognitive skills are: Identifying, Discriminating, Differentiating, Comparing, Perspective-taking, Relating, Coordinating and Taking into account (Van Manen, Prins & Emmelkamp, 2001). This test consists of 7 short stories with corresponding pictures and each story contains 8 questions that represent the eight social cognitive skills. It takes approximately 30 minutes to complete the test. For this study it is decided to use the short version of the SCVT (version A), consisting of three stories. The reliability and construct validity of SCVT are judged as sufficient by the COTAN who assesses the psychometric properties of the Dutch versions of psychological tests.

**Outcome measure: Working memory**

**Instrument: Chessboard task** performed by children

The chessboard task is a recently developed working memory performance task on the computer based on the Letter – Number sequencing task from the Wechsler Adult Intelligence Scale (WAIS; Wechsler, 1958) and the Corsi Block Tapping Task (Corsi, 1972). The task assesses the ability to manipulate/reorganise and maintain visual-spatial information relevant for the task at hand (Dovis et al, 2011). On the computer screen, a sequence of stimuli (squares that light up) is presented one by one on a four by four grid with green and blue squares in a chessboard formation. Each stimulus lights up for 900ms, after which a 500ms inter-stimulus interval is presented. The participants respond by clicking on the lit up squares, ordering the presented stimuli by clicking on the green squares first, and then the blue squares. The time it takes to administer this test depends on the amount of trials presented. Psychometric characteristics are unknown.

**Outcome measure: Working memory**

**Instrument: BRIEF** filled out by parents/legal guardians and teachers (subscale: Working memory) (**Attachment.G**)

The Behaviour Rating Inventory of Executive Function (BRIEF) is a screening list to assess executive functioning in the home and school environment in children 5-18 years of age. The questionnaire contains 86 items in eight non-overlapping clinical scales and two validity scales. These theoretically and statistically derived scales form two broader Indexes: Behavioural Regulation (three scales: Inhibit, Shift, Emotional Control) and Metacognition (five scales: Initiate, Working Memory, Plan/Organise, Organisation of Materials, Monitor), as well as a Global Executive Composite score. The answers are scored on a 3-point Likert scale (never – sometimes - often). It takes approximately 30 minutes to fill in the questionnaire. The Dutch version of the BRIEF contains norms of a representative sample of

children in regular education. The BRIEF has a good reliability and construct validity (Elling & Minderaa, 2010).

### **Outcome measure: Self-efficacy**

**Instrument: Self-constructed questionnaire** filled out by children (**Attachment.H**)

This questionnaire is designed to get a better understanding of the kind of things that are difficult for children with ADHD. Children are asked to rate on a scale from 0 to 100 how certain they are that he or she masters certain skills concerning time management, planning and social behaviour.

### **6.1.3 Primary outcome measures**

The three primary outcome measures are:

- Planning / organisation – measured by BRIEF (subscale plan/organise), total score of the parents;
- Time management – measured by self-constructed questionnaire, total score of the parents;
- Social behaviour – measured by SSIS (subscale cooperation), total score of parents.

### **6.1.4 Additional measures**

#### **Exploratory in-game measurements**

HealSeeker is attached to a database which files the anonymised game results of the children. Examples of variables that are measured are play date, play time and within game progression.

#### **Baseline measurement of game experience and use**

**Instrument: Self-constructed questionnaire** filled out by parents/legal guardians (**Attachment.J**)

This questionnaire examines the experience level of children concerning gaming and computer use.

#### **Post-test measurement of satisfaction**

**Instrument: self-constructed questionnaire** filled out by parents/legal guardians and children (**Attachment.K – parents and Attachment L - Children**)

Parents and children can indicate how satisfied they are about the

game on the satisfaction questionnaire. Answers are scored on a 10-point Likert scale.

## **6.2 Randomisation, blinding and treatment allocation**

Randomisation will be used to minimize bias in the assignment of subjects to treatment groups to increase the likelihood that known and unknown subject characteristics (e.g., demographic and baseline characteristics) are equally balanced across treatment groups (1:1), and to enhance the validity of statistical comparisons across treatment groups.

The randomization list will be stratified by site and gender using randomly permuted blocks.

Randomisation to the immediate and delayed treatment group condition will occur after collection of baseline data and confirmation of eligibility in the web-based ECD system.

The randomization process will be automated and based on a pre-specified computer-generated randomization list. A randomization number will be assigned online using the next available number on the randomization list corresponding with the site and gender of the subject. The trial will be open-label. Due to the nature of the intervention and time frame, it will be obvious for participants, their parents and teachers and the site staff to which treatment group they are allocated. All efforts are made to keep the assessor blind. If a child spontaneously tells the assessor his or her treatment condition, this will be registered.

## **6.3 Signaling resistance**

### *Measurements*

Possible (nonverbal) resistance of children during measurements will be evaluated in different manners. The investigator will observe children on signals of restlessness and/or emotional reactions as a consequence of filling out the questionnaires. Examples of emotional reactions are anger, sadness, fear or panic. In case of such emotional reactions the investigator will try to find out where this resistance is coming from and will calm down the child for example by giving more information about the trial. In addition it will be explained to the child that he/she does not have to fill out the questionnaires if he/she does not want to do that. Measurements will be registered as discontinued as a consequence of resistance (see also "Behaviour code of resistance with regard to participation in medical scientific research" at [www.ccmo.nl](http://www.ccmo.nl) established by the Dutch National Association of Paediatricians). The investigator will emphasize that the child can leave the study at any time for any reason if they wish to do so without any consequences. During these measurements children are supervised by a investigator who has a master degree in pedagogy or psychology. They are able to recognise restlessness and/or emotional reactions and will be alert on these signals during measurements.

### *Intervention period*

Parents/legal guardians will be informed about recognising signals of resistance and how to cope and react on it. In addition, parents/legal guardians will be individually informed by the investigator during the T0 measurement about how they think their child will react on the game and what form of resistance they expect. Parents/legal guardians and investigator decide upon the way parents/legal guardians will cope and react on the resistance of their children. It is possible that the investigator performs a home visit in which he/she explains the child how the game works. As such the child may be less fearful to play the game at home. When a child does not want to play the game and shows signals of restlessness or resistance, study participation will be registered as discontinued as a consequence of resistance. During the intervention period investigators are available through mail and by phone to answer questions parents/legal guardians may have. It is expected that resistance is minimal in this study during the intervention period because these children are highly motivated to play a serious game. Through good coaching and availability of the investigator resistance can be minimised. The investigator will emphasise that parents/legal guardians and their child can leave the study at any time for any reason if they wish to do so without any consequences.

### **6.4 Withdrawal of individual subjects**

Parents/legal guardians and children can leave the study at any time for any reason if they wish to do so without any consequences. This is also explicitly formulated in the information letter for parents/legal guardians and children. It will be stressed that withdrawal from the study does not have any consequences for the treatment as usual children follow within their mental health care institution. In the case that parents/legal guardians and children decide to leave the study, this means that no further information will be gathered from the child. It is expected that withdrawal is minimal in this study during the intervention period because these children are highly motivated to play a serious game. Through good coaching and availability of the investigator withdrawal can be minimised. Withdrawal will be registered as an indication of treatment compliance.

### **6.5 Replacement of individual subjects after withdrawal**

Subjects will not be replaced after withdrawal.

### **6.6 Follow-up of subjects withdrawn from treatment**

No follow-up will be conducted with subjects withdrawn from treatment.

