## **5.2 Use of co-intervention**

In addition to treatment as usual (i.e. pharmaceutical, cognitive-behavioural therapy and/or psycho educational sessions), all children will receive the HealSeeker game during the research period. The first group will immediately start playing Healseeker after baseline measurements and the second group will start 10 weeks later. The treatment as usual is offered by the mental health care institution where the child is registered. This treatment has to be stable for two months while the study continues and preferably between measurement moments. The treatment as usual will be registered and monitored by a general questionnaire which is answered by the parent/legal guardian.

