## 8. STATISTICAL ANALYSES

The modified ITT analysis set will include all randomized subjects who have both a baseline and at least one post-baseline efficacy assessment. Hochberg procedure (Biometrika, 1988) will be used to control the experiment-wise alpha level at 0.05 for the multiple primary endpoint analyses. All tests will be two-sided.

For all outcome measures descriptive statistics (mean, SD, median and range) as well as their changes from T0 (Baseline) will be calculated by treatment group. Within-group comparisons of changes at T1 (Week 10) from T0 will be conducted in both groups.

To assess whether effects are maintained after stopping the game, within-group comparisons of changes at T2 (Week 20) versus T1 will be performed in the Immediate group. To assess effects of game after waiting period, within-group comparison of changes at T2 versus T1 will be conducted in the delayed group.

An analysis of covariance (ANCOVA) model that includes treatment, site and gender as factors and baseline as covariate, will be used for the primary outcome measures to estimate the difference between the two groups in changes from T0 at T1.

Exploratory analyses may be conducted as deemed appropriate to examine whether intervention effects vary as function of demographic and baseline characteristics (e.g. age, gaming experience), to explore correlations between different measures, to investigate potential mediating effects (e.g. working memory, self-efficacy).

All adverse events will be listed. Special attention will be given to those subjects who discontinued due to an adverse event.

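### Stopping the game is treated as leaving the study, so children who resist it before T1 lose their primary outcome data, by a route that exists only in the immediate arm

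*Protocol*

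**What the plan says.** Four parts of the protocol act together.

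- **Section 6.3 (Intervention period):** "When a child does not want to play the game and shows signals of restlessness or resistance, study participation will be registered as discontinued". What ends is participation in the study.
- **Section 6.4:** once a family leaves the study, "this means that no further information will be gathered from the child". The same section adds: "Withdrawal will be registered as an indication of treatment compliance". This uses an event of study participation as a measure of adherence.
- **Sections 6.5 and 6.6:** "Subjects will not be replaced after withdrawal", and "No follow-up will be conducted with subjects withdrawn from treatment". The heading and sentence of 6.6 refer to treatment, so stopping the game is enough to end assessment.
- **Section 8:** "The modified ITT analysis set will include all randomized subjects who have both a baseline and at least one post-baseline efficacy assessment". The primary ANCOVA is used "to estimate the difference between the two groups in changes from T0 at T1".

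On timing, section 5.2 says: "The first group will immediately start playing Healseeker after baseline measurements and the second group will start 10 weeks later". Sections 9.5 and 9.6 speak of withdrawing from the intervention, so the protocol knows the distinction between intervention and study, but sections 6.3 to 6.6 do not use it.

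**The concern.** Randomisation protects the T1 comparison only if the children measured at T1 are still comparable between arms. Here a child's reaction to the intervention decides whether the primary outcome is collected, and before T1 only one arm can have that reaction. A delayed-arm child who would have resisted the game in the first ten weeks is never asked to play, is measured at T1 and stays in the analysis. The matching child in the immediate arm is not measured.

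If such children tend to improve less on parent ratings, for whatever reason, removing them from one arm raises that arm's mean change without any effect of the game. This is a rule on data collection. An SAP can model missing T1 values, but it cannot recover ratings that the protocol says not to collect.

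**Working it through.** **1. Does the chain hold?** Resistance ends participation (6.3). No follow-up takes place after withdrawal from treatment (6.6). The first post-baseline efficacy assessment is T1 at week 10 (Table 1), so a child stopped before then has none and cannot enter the modified ITT set (8). A delayed-arm child who resists after week 10 already has T1 and remains. The game-related route is therefore one-sided for the T0 to T1 contrast.

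**2. Is the loss avoidable?** All three primary outcomes are parent-rated (6.1.3). A child's unwillingness to play does not prevent a consenting parent from completing them. The repeated parent scales in Table 2 take 5 + 10 + 10 + 15 = 40 minutes per visit.

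**3. The plan's own figure (4.5).** Difference 8, SD 16, two-sided 5%, 78 per group: power is 87.7% by the normal approximation and 87.3% by the t-test. The stated 87% reproduces, and the sample size arithmetic is not at fault. Enrolling 85 to keep 78 implies an allowance of 7/85 = 8.2% for dropout from all causes.

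**4. Possible size.** Inputs from the protocol: SD 16, 85 per arm, the 8.2% allowance, and the pilot's 42 children included with 36 analysed on complete data (6/42 = 14.3% incomplete). Assumed, because the protocol gives neither: *k* of 85 immediate-arm children stop before T1, and their change would have been *g* points worse than that of the other children. Suppose there is no true effect and the same share of such children sits, measured, in the delayed arm. Then:

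- spurious benefit = (k/85) × g
- SE = 16 × √(1/(85 − k) + 1/85)
- type I error = Φ(−1.96 + bias/SE) + Φ(−1.96 − bias/SE)

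Worked case, k = 7 and g = 16: bias = 0.0824 × 16 = 1.32; SE = 16 × √(1/78 + 1/85) = 2.51; bias/SE = 0.525; type I error = 0.0757 + 0.0065 = 8.2%.

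| Lost from immediate arm | g = 4 | g = 8 | g = 16 |
|---|---|---|---|
| 0 | 0 (5.0%) | 0 (5.0%) | 0 (5.0%) |
| 4 of 85 (4.7%) | 0.19 (5.1%) | 0.38 (5.3%) | 0.75 (6.1%) |
| 7 of 85 (8.2%) | 0.33 (5.2%) | 0.66 (5.8%) | 1.32 (8.2%) |
| 12 of 85 (14.1%) | 0.56 (5.6%) | 1.13 (7.3%) | 2.26 (14.3%) |

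Entries are points of spurious benefit, with per-test two-sided type I error in brackets, before the Hochberg procedure. The last row is the nearest whole number of children to the pilot's 14.3%.

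**5. The same rule with a true effect.** If children who play gain 8 and those who stop gain 0, the planned set estimates 8.0 whatever the stop rate. With everyone followed, the effect is 8 × (1 − 7/85) = 7.34 at k = 7 and 8 × (1 − 12/85) = 6.87 at k = 12.

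**The case against.** **A reader might infer that the rule removes non-responders.** The text does not say so. The trigger in 6.3 is unwillingness to play together with signs of restlessness or resistance, not lack of improvement. A child who plays little, or plays without benefit, and is not withdrawn keeps the T1 visit. The analysis set in section 8 has no adherence condition. So it also goes too far to describe the immediate arm at T1 as only those who kept playing.

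**A reader might infer that only the immediate arm loses children.** Section 6.4 lets any family leave at any time for any reason, including during ten weeks of waiting without the game. Only the game-related route is one-sided, and the net direction from all losses is not known.

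**The loss fractions are borrowed.** The 8.2% is an allowance for all dropouts in both arms. The pilot's 14.3% is incomplete data for unstated reasons, pooled over two groups that both had the game. Assigning either wholly to game resistance in one arm gives an upper value. The 4 to 16 point deficit has no source in the protocol.

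**Some evidence points to a small problem.** The protocol reports that 94% of pilot children liked playing and that the pilot's intention-to-treat results were similar to those from complete data. Section 6.4 expects little withdrawal. These points bear on likely size, although the pilot's intention-to-treat method is not described and section 4.5 still budgets for dropout.

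All of this limits the claim about size and direction. None of it breaks the chain from resistance to missing T1, and no passage offers a way to retrieve the data. If few children stop, following them costs almost nothing.

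**Conclusion.** The point holds as a fault in data collection. Sections 6.3, 6.4 and 6.6 do not separate stopping the game from leaving the study, so primary outcome data are given up for children who resist or are withdrawn from the game, by a route open in the immediate arm only. The T1 contrast may be biased, plausibly in favour of the game, but the protocol does not establish the direction.

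The size rests on assumptions. With 0 to 8.2% of the immediate arm lost and a deficit of 4 to 16 points, the spurious benefit is 0 to 1.3 points against a planned difference of 8, with per-test type I error between 5% and about 8%. The figures of up to 2.3 points and about 14% require a loss as large as the pilot's whole incomplete share, all of it game-related and in one arm, and a full 1 SD deficit; treat them as an extreme case. Confidence is high in the textual chain and low in the size. Label: cheap improvement, to be made before enrolment because missed T1 ratings cannot be recovered.

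**What to change.** - **6.3:** record that the child has stopped playing as an event separate from leaving the study.
- **6.4:** confine the rule of no further data to families who leave the study or withdraw consent for data collection, and record stopping the game separately as adherence.
- **6.6:** state that, unless consent for data collection is withdrawn, T1 and T2 parent ratings are sought on schedule, along with teacher ratings and, if the child is willing, the child tasks.
- **8:** state that these children stay in the arm assigned for the primary ANCOVA. The set as defined already allows this once they have a T1 value.

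Nothing here changes when or why a child may stop playing, or the family's right to leave.

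The cost is protocol wording plus about 40 minutes of parent questionnaires per visit for the few families concerned. Some will still not respond, so some T1 values will remain missing.
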